## Abstract

**Background:**

Anxiety, mood, and substance use disorders have significant social and economic impacts, which are largely attributable to their early age of onset and chronic disabling course. Therefore, it is critical to intervene early to prevent chronic and debilitating trajectories.

**Objective:**

This paper describes the study protocol of a CONSORT (Consolidated Standards of Reporting Trials)-compliant randomized controlled trial for evaluating the effectiveness of the Mind your Mate program, a mobile health (mHealth) peer intervention that aims to prevent mental health (focusing on anxiety and depression) and substance use problems in adolescents.

**Methods:**

Participants will consist of approximately 840 year 9 or year 10 students (60 students per grade per school) from 14 New South Wales high schools in Sydney, Australia. Schools will be recruited from a random selection of independent and public schools across the New South Wales Greater Sydney Area by using publicly available contact details. The intervention will consist of 1 introductory classroom lesson and a downloadable mobile app that will be available for use for 12 months. Schools will be randomly allocated to receive either the mHealth peer intervention or a waitlist control (health education as usual). All students will be given web-based self-assessments at baseline and at 6- and 12-month follow-ups. The primary outcomes of the trial will be the self-reported use of alcohol and drugs, anxiety and depression symptoms, knowledge about mental health and substance use, motives for not drinking, and willingness to seek help. Secondary outcomes will include positive well-being, the quality of life, and the impact of the COVID-19 pandemic. Analyses will be conducted using mixed-effects linear regression analyses for normally distributed data and mixed-effects logistic regression analyses for categorical data.

**Results:**

The Mind your Mate study was funded by an Australian Rotary Health Bruce Edwards Postdoctoral Research Fellowship from 2019 to 2022. Some of the development costs for the Mind your Mate intervention came from a seed funding grant from the Brain and Mind Centre of the University of Sydney. The enrollment of schools began in July 2020; 12 of 14 schools were enrolled at the time of submission. Baseline assessments are currently underway, and the first results are expected to be submitted for publication in 2022.

**Conclusions:**

The Mind your Mate study will generate vital new knowledge about the effectiveness of a peer support prevention strategy in real-world settings for the most common mental disorders in youth. If effective, this intervention will constitute a scalable, low-cost prevention strategy that has significant potential to reduce the impact of mental and substance use disorders.

**Trial Registration:**

Australian New Zealand Clinical Trials Registry ACTRN12620000753954; https://www.anzctr.org.au/Trial/Registration/TrialReview.aspx?id=379738&isReview=true

**International Registered Report Identifier (IRRID):**

DERR1-10.2196/26796

## Introduction

### Background

By 2030, the global health care costs associated with mental illness and substance use are predicted to be more than the pooled costs attributed to cancer, diabetes, and respiratory diseases [1]. Although the provision of widespread treatment is essential, if we are to significantly affect population health, effective prevention is also critical. Recent population data show that mental health problems among adolescents are rising [2], indicating that current prevention approaches do not prevent population level increases. Both mental health symptoms and substance use, begin and escalate during adolescence [3], with even small elevations in adolescence increasing the likelihood of developing a full-blown mental disorder later in life [4]. From the ages of 13 to 24 years, there is an increased susceptibility to the development of mental illness and substance use problems, with longitudinal life course studies indicating that transitions from childhood to adolescence and from adolescence to young adulthood are marked by significant increases in mental and substance use disorders [3]. This makes adolescence a critical time to intervene and prevent these problems using scalable and novel prevention approaches.

The social network theory has demonstrated that peers have a powerful influence on health behaviors, including mental health [5] and substance use [6]. Studies using social network analysis are beginning to uncover the mechanisms by which health behaviors, such as mental health symptoms and alcohol use, diffuse and spread through peer groups [7-9]. This approach is currently used to better understand the development and prevention of these problems. Several studies using a large nationally representative US data set (AddHealth) found that both friendship connections and peer influence function are causal factors that influence adolescents’ health risk behaviors [10,11]. The size of this influence is substantial, with a 10% increase in the proportion of adolescent peer group members who drink alcohol, resulting in a 4% increase in individual drinking [12]. Furthermore, social connections among peers are important determinants of behavior, with a one SD increase in (1) friends’ prior drinking increasing the odds of an adolescent binge drinking by 30% and (2) friends-of-partner drinking increasing the odds of binge drinking by 81% [13]. Research has also started to uncover the role of peer groups in the etiology of mental health symptoms, with processes such as corumination between peers actively increasing the risk of developing poor mental health, such as depression [14,15]. Conversely, it has recently been speculated that interventions providing positive support and scaffolding through the power of peers to develop prosocial, healthy behaviors during adolescence could have significant benefits for adolescent health and development [16].

Current prevention programs for adolescent mental health and substance use typically show modest effect sizes and limited implementation [17]. Universal school-based programs delivered to all adolescents, regardless of the level of risk, have been shown to demonstrate small to moderate effects in reducing alcohol misuse [18,19] and levels of anxiety and depression [20,21] and increasing mental health literacy [22]. As many current mental health prevention approaches largely represent adaptations of treatment approaches that were originally designed for adults, it is unclear how the unique developmental needs of adolescents have been taken into account in the design of these programs [23]. Adolescents are hypersensitive to social stimuli and are more susceptible to peer feedback on decision-making. Therefore, it is critical to consider the substantial role of peers in designing effective prevention strategies [23]. Furthermore, a recent review [17] of mental health interventions in schools in *The Lancet* identified the development and evaluation of peer-led models as a significant gap in the field.

In addition to influencing behavior, peers play an important role in identifying and facilitating access to support for friends with mental health and substance use issues. Currently, most young people experiencing difficulties with mental health and/or substance use will not seek help [24]. One study found that approximately only 20% of adolescents (aged 14-15 years) sought help for depression, whereas only 3% sought help for alcohol or other drug problems [25]. Those who sought help for substance use cited that friends were their main source of support, followed by parents or health professionals as reported by a much smaller proportion [25]. However, adolescents may not be equipped with the knowledge, skills, or awareness of appropriate referral services to provide adequate support to their peers when mental health and substance use problems arise. Thus, empowering adolescents to help their peers is not only critical to ensure that the advice and support received is appropriate, but can also facilitate help seeking for those providing support [25].

One existing, evaluated peer training program for adolescents is Teen Mental Health First Aid. Developed in Australia, this program includes three in-school sessions with trained facilitators to increase mental health literacy and reduce stigma, with separate courses for students in years 7-9 (ages 12-14) and years 10-12 (ages 15-17) [26,27]. These programs have shown promising effects in increasing help-seeking intentions and confidence to support friends and reducing stigma around mental health [26,27]. However, the program’s impact on mental health symptoms has yet to be evaluated and it uses face-to-face delivery from external trainers, potentially limiting its scalability.

Current adolescents have grown up in a world with unequivocal access to technology and information. In Australia, 91% of teenagers (aged 14-17 years) own a mobile phone, and 94% of these phones are internet-connected smartphones [28]. One key opportunity for the prevention of mental disorders is the possibility of harnessing such mobile technology to deliver easily accessible prevention strategies that can be widely implemented at low cost, in a format that is acceptable to and engaging for adolescents. Adolescents use their phones to communicate with their peers daily and regularly access web-based information. In a US survey, 89% of teenagers reported being on the web *several times a day* to *constantly* [29], with SMS text messaging as the dominant form of communication among peers on a daily basis [30]. Despite the recognition of the key role that peers play in health behavior and the frequent use of digital technologies by adolescents, scientifically evaluated digital peer interventions are lacking, with limited evaluations of current web-based or mobile programs available for adolescents.

To address these gaps, the Mind your Mate intervention was developed, a novel mobile health (mHealth) intervention aimed at upskilling and empowering adolescents to better support their peers on issues related to mental health, alcohol, and other drug use.

### Aims, Objectives, and Hypotheses

This study aims to evaluate the effectiveness of Mind your Mate program among adolescents through a cluster randomized controlled trial (RCT) conducted in partnership with secondary schools. We hypothesized that the Mind your Mate intervention will be more effective than the active control group (health education as usual) in (1) delaying the uptake of alcohol and other drugs; (2) reducing anxiety and depression symptoms; (3) increasing knowledge about mental health, alcohol and other drugs; and (4) increasing help-seeking behavior.

## Methods

### Ethics Approval and Consent to Participate

The study was approved by the University of Sydney Human Research Ethics Committee, Australia (project number: 2020/054). Both active parental consent and active participant (student) consent were required before students could participate in the study.

Access to schools was granted by the New South Wales (NSW) Department of Education and Communities (State Education Research Applications Process 2020130).

### Study Design

This trial is registered with the Australian New Zealand Clinical Trials Registry (trial number: ACTRN12620000753954).

To determine the effectiveness of the Mind your Mate intervention, a cluster RCT will be conducted among year 9 or year 10 students (aged approximately 14 years) at 14 independent and public secondary schools in NSW from 2020 to 2021. Cluster randomization will be used to avoid contamination of the controls by the intervention group through student communication. Schools will be randomly allocated to either the Mind your Mate intervention condition or the active control condition (health education as usual). Figure 1 summarizes the anticipated recruitment, randomization, and assessment of the participants.

**Figure 1 figure1:**
[figure not shown]
Anticipated recruitment, randomization, and assessment of participants based on the CONSORT (Consolidated Standards of Reporting Trials) guidelines.

### Sample Size Calculations

This trial is powered to detect intervention by time interactions in longitudinal cluster RCTs. To allow for comparisons between the two conditions, 6 schools (with at least 60 students) in each of the 2 intervention groups were required, giving a total of 12 schools (with at least 720 students). This would achieve 80% power to detect a standardized between-group mean difference of 0.2 in outcomes at the end of the trial with three measurement occasions (*P*=.05). An effect size of 0.2, which is comparable with previous trials of anxiety, depression, and substance use prevention programs [20,21,31-34], would have substantial benefits at the population level according to economic modeling [35]. It is anticipated that the majority of students in the year group of participating schools will take part in the study, based on participation rates found in previous school-based trials conducted by the research team [36-39]. To account for school dropouts during the trial, which are expected to be approximately 10% based on similar previous school-based trials [40], this study will recruit 14 schools (with at least 840 students).

### Procedure

#### Inclusion and Exclusion Criteria

Eligible participants will be all year 9 or year 10 students (aged approximately 14-15 years) attending participating schools that own a smartphone. Providing smartphones or laptops to study participants with technological barriers was not possible because of time and budget constraints. Mobile and internet literacy will be assumed. Students will be required to provide active informed consent, and only students with active parental consent will be eligible to participate.

#### Recruitment of Schools

A random selection of independent and public schools across the NSW Greater Sydney Area (Greater Capital City Statistical Area, 1 Greater Sydney) [41] will be approached through publicly available contact details. The study will be advertised through the researchers’ networks and the Matilda Center’s social media sites. Schools that took part in focus groups for feedback on mobile app development, as part of the Mind your Mate Development Study (University of Sydney Ethics Approval 2019/723) will also be approached. School principals will be sent an invitation letter via email outlining the aims of the study and seeking permission to implement the study in their school. Schools will then be followed up through phone calls by the research team.

Schools principals who consent to their school taking part will be asked to identify an appropriate staff member and inform the research team on how to liaise with this staff member with regard to the trial.

#### Randomization

Following the school principal’s approval, randomization and stratification according to gender will be conducted by a biostatistician external to the research team using the blockrand function in R (R Core Team). The school gender mix for stratification will be coeducational, predominately male, or predominately female, and the threshold for predominately male or predominately female will be at >60%. Half of the schools (n=7) will be randomly allocated to the Mind your Mate intervention condition and half (n=7) to an active control group (health education as usual). Similar to school-based interventions of this kind, students and teachers will not be blinded to intervention allocation.

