#### Informed Consent

Participating schools will be asked to send information and active (opt-in) consent forms to parents or guardians of year 9 or year 10 students via hard copy or electronically. Students who receive parental consent will be provided with a web-based participant information statement and consent form and will be required to actively consent before beginning the study. Students who do not consent or who do not receive parental consent to participate in the research trial will still be offered access to the content of the program; however, they will not be prompted to complete assessment surveys, and no data will be collected from those individuals.

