#### Classroom Lesson

The Mind your Mate classroom lesson will be web-based through the study website by teachers of the participating schools. Teachers will be provided with an implementation guide containing instructions for accessing the survey, classroom lessons, and an outline of the content links to the NSW Personal Development, Health, and Physical Education Syllabus.

The classroom lesson will take approximately 40 minutes to complete and will be conducted after the students have completed the baseline survey. The lesson introduces common mental health and substance use problems encountered by young people and discusses the concept of supporting peers through animated examples, quizzes, and interactive activities (Figure 2 for example screenshots of these components). The lesson concludes with a video tour of the app’s features and instructions for students to download the app onto their mobile device. Students were instructed to use the mobile app as needed over the following 12-month period.

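### As written, schools are randomised on the principal's approval and without blinding, and nothing withholds allocation until opt-in consent and the baseline survey are complete, so who enters can differ by arm

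*Protocol article*

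**What the plan says.** All references are to the protocol article.

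- **Trigger for allocation (Randomization).** "Following the school principal’s approval, randomization and stratification according to gender will be conducted by a biostatistician external to the research team". Seven schools go to each arm. No other step is named as a condition.
- **Blinding (Randomization).** "students and teachers will not be blinded to intervention allocation".
- **Parental consent (Informed Consent).** "Participating schools will be asked to send information and active (opt-in) consent forms to parents or guardians".
- **Student consent (Informed Consent).** Students with parental consent "will be required to actively consent before beginning the study".
- **Eligibility (Inclusion and Exclusion Criteria).** "only students with active parental consent will be eligible to participate".
- **Students without consent (Informed Consent).** They may still use the program content, but "they will not be prompted to complete assessment surveys, and no data will be collected from those individuals".
- **Lesson (Classroom Lesson).** It "will be conducted after the students have completed the baseline survey".
- **Analysis (Statistical Analysis).** Intention-to-treat, mixed models for intervention-by-time effects, baseline primary outcomes as covariates, and tests of baseline equivalence. The section presents the covariates as a guarantee that baseline differences are dealt with.
- **Progress (Results).** At submission, 12 of 14 schools were enrolled and baseline assessments were under way.

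**The concern.** In a cluster trial, randomisation makes the schools comparable. It makes the students comparable only if their entry does not depend on the arm. Here entry needs two individual consents, and the consent forms go out through schools whose staff are not blinded. If the arm is known by then, staff effort in chasing forms, parents' willingness and students' interest can all depend on it. Control schools have no app during the trial, so what is on offer differs by arm. Students who know their arm might also answer the baseline self-report differently.

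At stake is a selection bias in symptoms and substance use, which plausibly relate to willingness to join. A larger sample does not shrink it. Because no data are collected on students who do not consent, it cannot be checked against those who stayed out.

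**Working it through.** The article gives no figure for this bias, so there is none to reproduce. The check has two parts.

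**1. Order of steps**

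| Step | What the article fixes | Order relative to allocation |
|---|---|---|
| Principal's approval | Precedes randomisation | Before |
| Parental opt-in | Run by schools already participating | Not stated; after, on the plain reading |
| Student consent | After parental consent, before starting the study | Not stated; after, on the plain reading |
| Baseline survey | Before the lesson | Not stated |
| School learns its arm | – | Not stated |

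The external biostatistician protects the allocation of schools. That does not protect the later entry of students, and no sentence closes the gap.

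**2. Possible size (illustration)**

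From the article: target 0.2 SD; 6 schools × 60 students = 360 per arm.

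Assumed, not from the article:
- Consent is unrelated to outcome in the control arm.
- In the intervention arm, log-odds of consent = a + ln(OR)·x, where x is the student's standardised propensity for the follow-up outcome. OR is 1.1 to 1.5 per SD.
- Overall consent is 40% to 80%.
- Baseline and follow-up correlate ρ = 0.6.

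The spurious arm difference at follow-up is m, the mean of x among consenters, found by numerical integration. The baseline mean then shifts by ρm. Adjusting for baseline removes ρ·ρm and leaves m(1 − ρ²) = 0.64m. A change-from-baseline contrast leaves m − ρm = 0.4m.

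| Consent | OR | m (SD) | After adjustment, 0.64m | Change contrast, 0.4m |
|---|---|---|---|---|
| 80% | 1.1 | 0.019 | 0.012 | 0.008 |
| 60% | 1.25 | 0.088 | 0.056 | 0.035 |
| 40% | 1.5 | 0.234 | 0.150 | 0.094 |

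Two limiting cases bound this. If selection acts only through the measured baseline score, adjustment removes it. If selected students differ by the same amount at baseline and follow-up, the intervention-by-time contrast is unaffected. What remains is selection related to change over time, plus any effect of knowing the arm on baseline answers, which this model does not cover.

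For scale, take a residual bias of 0.05 SD in a simple comparison of follow-up means, with SE = √[(2/360)(1 + 59·ICC)]. At an assumed ICC of 0, SE = 0.075 and the nominal two-sided 5% error becomes about 10%. At an assumed ICC of 0.02, SE = 0.110 and it becomes about 7%.

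**The case against.** The strongest reply is that the order is inferred. Principal approval sets the earliest point for randomisation; it does not say that allocation precedes consent or baseline, or that anyone knows the arm when consenting. The flow diagram is not available in the text reviewed, and an article may leave the timing of release to the full protocol. This stands as a limit on wording. A reader might infer that the baseline survey follows allocation as a stated fact, but the article does not say so. The concern survives because the article does state the trigger, the consent route and the lack of blinding, and nothing in it withholds allocation.

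Second, safeguards exist. Baseline outcomes are covariates, the survey precedes the lesson, and baseline equivalence is examined. A reader might conclude that adjustment is useless if the survey came after allocation. That is wrong: differential entry on symptom level shows in baseline scores, and adjusting for them reduces it. But the reduction is partial, so the article's assurance is too strong. Equivalence tests see entrants only.

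Third, offering the content without research consent weakens one arm-specific motive to opt in. That is fair. It does not address staff effort or arm-influenced answers.

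Fourth, it is tempting to assume a difference in consent rates, convert it to a shift in means and quote it as a share of 0.2 SD. The documents do not support such a figure. They give no consent rates, and the trial is powered for an intervention-by-time contrast, from which a stable difference would largely cancel.

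**Conclusion.** The concern holds as a risk that the plan as written leaves open, not as a demonstrated bias. Nothing in the article prevents student entry, and possibly baseline answers, from depending on the arm. Intention-to-treat covers only students who entered, and baseline covariates repair the problem in part.

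The size is unknown. The middle illustration leaves about 0.06 SD after adjustment, or 0.04 SD on a change contrast, which is a modest fraction of the 0.2 SD target. The assumed range runs from about 0.01 to 0.15 SD after adjustment. These values depend wholly on the assumed consent model and ρ = 0.6. For the intervention-by-time contrast, the bias matters mainly where selection relates to change over time or where knowing the arm affects baseline answers.

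The conclusion rests on the plain reading of the sequence. If consent and baseline in fact came before allocation was made known, a sentence saying so would settle it.

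**What to change.** - **Schools not yet allocated or not yet told their arm:** have the external biostatistician release a school's allocation only after its consent forms are returned and its baseline survey is completed. The lesson already follows the survey, so delivery does not change. The cost is shorter timetable notice for schools. With 12 of 14 schools enrolled and baseline under way at submission, this may reach few of them.
- **Schools already allocated:** state the actual order of allocation, consent and baseline; report eligible, invited and consenting numbers by school and arm; and add recruitment bias to Strengths and Limitations, which discusses self-report but not this. The cost is a few sentences and a table.
- **Statistical Analysis:** say that baseline covariates reduce measured baseline imbalance, rather than that they take care of all of it.

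A sensitivity analysis limited to schools whose consent preceded allocation is not recommended: on the plain reading there would be few or none.
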